## Abstract

**Background:**

This research protocol for the study ATICC (Addiction, Trauma and Immigration, prevention and Cross-Cultural support for care with the Grand Est youth network) aims to model the complex interrelations between trauma, substance use behaviors, migration and representations of mental health among vulnerable youth residing in Transitional Housing for Young Adults. This study focuses on a specific and underexplored population, many of whom have experienced traumatic events and/or complex migratory trajectories. The ultimate objective of this research is to develop transferable models of understanding that can inform the design of prevention and support programs tailored to this demographic.

**Methods/Design:**

We adopt a tripartite methodology approach: (1) a cross-sectional study using standardized questionnaires to identify factors associated with substance use, trauma, and barriers to healthcare access; (2) an in-depth qualitative study based on semi-structured individual interviews with substance users, exploring their subjective experiences and perceptions related to substance use and mental health care; and (3) a longitudinal interventional study involving various configurations of focus groups open to residents of transitional housing structures, aiming to assess the impact of these group sessions on participants’ psychological well-being and attitudes toward care. Quantitative analyses will include descriptive and multivariate statistical tests using R, while qualitative data will be analyzed through thematic analysis with NVivo. The effectiveness of the group intervention will be evaluated using pre/post-tests, mixed models, and appropriate statistical corrections.

**Discussion:**

Analyses are expected to identify key psychosocial factors influencing addictive behaviors and mental health, highlight cultural and structural barriers to care, and assess the psychological benefits of the group intervention. The ATICC study aims to contribute to the development of culturally adapted prevention and support models for young adults in precarious situations. The results should assist healthcare professionals and policymakers in designing evidence-based interventions that effectively address the specific needs of this population.

**Trial registration:**

This study is registered with the Biomedical Research Identification Number (n°ID-RCB) assigned in France by the National Agency for the Safety of Medicines and Health Products (ANSM): 2024-A01534-43, and have received the approval from the committee for the protection of persons (CPP) Ile-de-France on November 18, 2024. Cette étude a également été déposée sur clinicaltrials (NCT06922721, date assigned April 10, 2025).

**Supplementary Information:**

The online version contains supplementary material available at 10.1186/s40359-025-02738-5.

## Background

In France, young adults facing precarious conditions can, under certain criteria, be accommodated into specific structures such as Transitional Housing Program (THP) (Foyers de Jeunes Travailleurs: FJT). These establishments provide support to individuals aged 16 to 25 who meet vulnerability criteria and have diverse life trajectories, including those transitioning from child welfare services, refugees, individuals experiencing social or familial ruptures, trainees, students, and persons with disabilities. The mission of the THP go beyond providing temporary accommodation; they actively assist young individuals in their professional integration and transition toward sustainable autonomy, as outlined by law no. 2002-2 and decree no. 2015 − 951. Therefore, they rely on a network of health, legal, and social resources to address young residents’ needs in areas such as health, budgeting, access to rights, and social life, in partnership with specialized social service actors [1].

Young adults within this demographic are particularly exposed to adverse circumstances, which can significantly impact their mental health [2]. These already challenging conditions have been further compounded by the profound and multifaceted effects of the COVID-19 pandemic, which has intensified the deterioration of mental health, particularly among young adults in precarious situations [3]. This deterioration has been notably driven by social isolation measures that disproportionately affected various groups, thereby exacerbating symptoms of anxiety and depression [4–6]. Furthermore, the pandemic has the potential to reactivate past traumas, especially among individuals with migratory backgrounds and those who have experienced challenging situations marked by familial separation [7].

The transition to adulthood, a period marked by significant psychological complexity [8], is often accompanied by various expressions of distress, including the use of psychoactive substances and engagement in addictive behaviors [9, 10]. The transition from adolescence to adulthood is characterized by the individuation process, which may reactivate issues related to past ruptures and attachment. These challenges can contribute to the development of addictive behaviors, often associated to deficits in the formation of primary bonds and difficulties in establishing interpersonal relationships [11]. From this perspective, addictive behaviors can be understood as manifestations of attachment disorders stemming from early developmental and environmental deficiencies [12]. Numerous studies have demonstrated that young adults who experienced trauma during childhood or adolescence face significantly higher risks of substance use disorders and associated health problems [13, 14]. These patterns of substance use emerge through intricate interactions among familial, social, psychological, and contextual factors [15].

For young individuals from migrant backgrounds, a substantial body of research highlights the protective effect of immigrant status [16–18]. However, this protective effect tends to diminish over time due to factors such as prolonged residence, precarious living conditions, experiences of discrimination, and acculturation-related stress [19–22]. Moreover, studies focusing on unaccompanied minors (UM)—a significant proportion of THP residents— underscore the notable vulnerability of this population to substance use. Research indicates a potential increase in substance use among individuals who had already engaged in such behaviors in their country of origin [23–25].

The described factors emphasize a critical need for mental health care among this population, raising complex issues at the intersection of social, economic, and health challenges. Due to stigma, lack of personalized support, and unfamiliarity with available resources, young residents in THP often exhibit reluctance toward seeking psychological care [26]. This hesitance appears to be particularly pronounced among youth from foreign cultural backgrounds. Extensive research has identified recurring barriers among migrant populations, including socio-economic factors such as low educational attainment, precarious living conditions, uncertain migration status, spiritual and religious beliefs, language barriers, and mistrust toward institutions perceived as remote or associated with control organizations [27, 28]. Furthermore, a systematic review [29], highlights additional obstacles and gaps in access to mental health services for refugees and asylum seekers within the European Union, such as long waiting times, insufficient availability of professional interpreters, and limited physical accessibility to services. As a result, cultural differences, stigma, and a lack of awareness of available services contribute to a significant gap between the mental health needs of this population and the care they receive [29]. Consequently, the staff at these facilities often report feeling ill-equipped to address the needs of the youth effectively, prompting a reevaluation of their practices and underscoring the necessity to enhance and expand foundational training and reexamine existing frameworks [26].

This situation underscores the need to reevaluate mental health support systems, particularly for young adults in vulnerable situations. It is within this context that our research project, ATICC (Addiction, Trauma, and Immigration: Transcultural Prevention and Support Toward Care within the Habitat Youth Network in the Grand Est Region), is situated. Conducted by researchers from the INTERPSY Laboratory (UR 4432) at the University of Lorraine, this study aims to deepen our understanding of the complex relationships between trauma, psychoactive and addictive substance use, migratory experiences, and mental health perceptions among vulnerable young adults accommodated in partner support structures and THP facilities affiliated with the Regional Union for Youth Housing (Union Régionale pour l’Habitat des Jeunes: URHAJ). The ultimate goal of this research is to develop transferable models of understanding that can inform the design of prevention and support programs. This study focuses on a specific, understudied population of vulnerable young adults, many of whom have experienced trauma and/or complex migratory trajectories. By integrating a transcultural perspective, it seeks to explore the individual and collective dynamics related to mental health and access to care, thereby addressing a critical gap in both research and practice.

In this article, we present the methodological characteristics of this research, which is built upon a solid institutional partnership framework and grounded in the contextual realities of the field, tailored to the specific needs of the target population. The study adopts a multidimensional approach, structured around a tripartite methodology that combines a quantitative cross-sectional study, a qualitative study, and an intervention-based longitudinal study. These methodologies aim to achieve several objectives: (1) To identify factors associated with addictive behaviors and their connections to various aspects of mental health and related representations. (2) To explore subjective representations and motivations underlying addictive behaviors among young people. (3) To understand the impact of migration on the life trajectories of youth and how cultural factors influence help-seeking behaviors. (4) To prevent substance use risks by demystifying mental health care representations and supporting young people in becoming autonomous in their help-seeking processes.

## Methods/design

This research project is therefore structured around three complementary phases of study (Table 1), each based on a distinct methodological approach:

A **cross-sectional study (study 1)** that relies on a quantitative approach, conducted through the dissemination of online standardized questionnaires and scales (see: Measures) to young adults residing in partner structures at both regional and national levels. Its objective is to identify factors associated with addictive behaviors and to explore the links between trauma, migratory trajectories, food insecurity, psychological distress and perceived representations and barriers to accessing psychological care. These tools enable the rigorous collection of quantitative data and a multidimensional assessment to model the relationships between factors associated with the psychological and social challenges faced by this population. This study provides insights into general statistical trends.A **qualitative study (study 2)** adopting an exploratory perspective and aiming an in-depth understanding of the representations, subjective experiences, and individual and relational dynamics associated with addictive behaviors and trauma. The qualitative study builds upon the findings of Phase 1 by collecting clinical insights that provide a deeper understanding of the subjective dynamics of participants dealing with substance use issues and the obstacles encountered in their life trajectories that shape their relationship with care services.A **longitudinal study (study 3)** structured around a group intervention called the “Well-Being coffee group”, which operates as an open group (8 to 12 participants per session), conducted over six sessions, each lasting 1.5 to 2 h, held in the evening (6–8 PM) once a month for six months. Participation is voluntary for young residents in THP. The study aims to evaluate the impact of this group discussion format on participants’ psychological well-being, their perceptions of mental health, and their access to care.
Participants are assessed at multiple time points (T0: prior to the program, T1: mid-program, T2: end of the program, T3: post-program follow-up). These longitudinal evaluations, based on standardized tools, will enable a detailed analysis of participants’ well-being progression and the specific effects attributable to the group intervention. This study is part of an action-research framework, integrating clinical intervention with the production of scientific knowledge while offering transferable recommendations for other support programs aimed at vulnerable young adults.

**Table 1 Tab1:** Summary table of the research methodology

	Study 1	Study 2	Study 3
Type of study	Quantitative	Qualitative	Longitudinale
Method	Cohort study using self-administered questionnaires	Semi-structured interviews Rorschach test Adult Attachment interview (AAI)	Group intervention Self-administrated questionnaires
Eligibility criteria	Participant aged > 18 Resident in a Housing center Fluent in French adult participants who are not under guardianship (tutelle) or curatorship (curatelle).	Participant aged > 18 Fluent in French Any substance user Migratory background	Same as study 1
Exclusion criteria	Minors Do not speak and read French Under Guardianship or Curatorship	Minors Do not speak and read French Under Guardianship or Curatorship	Minors Do not speak and read French Under Guardianship or Curatorship
Main Outcomes	Substance use prevalence Mental health representations Mental health aspects (anxiety, depression) Childhood trauma	Substance use, trauma and migration trajectory (semi-structure interview) Attachment style (AAI tool) Psychological functioning (Rorschach test)	Substance use Perception of mental health care Wellness
Analysis	Quantitative analysis	Thematic analysis	Quantitative and qualitative analysis

### Participants

#### Study 1

We based our calculations on an approximate population size of 60,000 young individuals supported throughout the previous year (Year N-1) across the entire territory. The margin of error was set at 5%, with a confidence level of 95%. We applied Cochran’s formula (Z² × p × (1-p) / E²) to determine the required sample size. Accordingly, the sample size necessary for this cross-sectional study is 382 respondents.

#### Study 2

We will base our qualitative study on a sample of 30 young volunteers recruited independently of the cross-sectional study, following the procedures outlined below. However, participant inclusion will continue until data saturation is reached. Data saturation will be considered achieved when the main themes emerge, meaning that all relevant themes necessary to address the research questions have been identified in the collected data.

#### Study 3

For this study, we estimate a strong effect size of 0.7 (Cohen’s d) with a significance level of 0.05. Based on these parameters, and using the software G*Power 3.1, we determined that 55 participants would be required for each group modality, resulting in a total of 165 participants. To account for an estimated 10% dropout rate, we will include 182 young individuals in the study.

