### Procedures

#### Study 1

A national deployment will be conducted in collaboration with all partners and youth centers. Recruitment will be facilitated via email distribution. Young residents of Youth transition Centers across the country will receive an email from the National Union for Youth Housing (Union Nationale pour l’Habitat des Jeunes: UNHAJ). This email will include detailed information about the research and a link to access the study. Upon accessing the study’s homepage, participants will encounter an introductory note outlining the study, its objectives, a contact point for further information, and a link to open the questionnaire. Clicking the link will direct them to a consent form with a binary choice: “Yes” or “No,” responding to the question: “Do you consent to participate in this research?“. Participants who select “Yes” will activate the questionnaire and proceed with the study, while those who select “No” will not be able to participate.

#### Study 2

The qualitative study will focus on a sample of young residents from all the structures involved in this research. Inclusion criteria require participants to be adults, French-speaking, and affected by substance use issues. Participants who consent to take part in the study, after reviewing the information notice provided at least 15 days prior to the first interview to allow for reflection, will meet with one of the investigators from the research team. The investigator will present the consent form, detailing the study’s objectives, methodology, duration, potential constraints, and foreseeable risks, while addressing any questions from the participant.

Each participant will undergo three sessions of approximately one hour each: a semi-structured interview, administration of the Rorschach test, and the Adult Attachment Interview (AAI). All interviews will be conducted by the same investigator who conducted the initial session to foster a trusting environment. The study in each structure will be conducted in a secure and confidential setting for participants. All three sessions will be audio-recorded using a voice recorder, transcribed, anonymized, and subsequently destroyed to ensure confidentiality.

#### Study 3

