### Data analysis

#### Study 1

The research team will conduct statistical analyses using R. The cross-sectional study will characterize the study population through descriptive and multivariate analyses (e.g., Chi-square/Fisher’s exact tests, correlation tests, ANOVA, etc.). We will adhere to the STROBE guidelines for epidemiological studies [58]. A significance level of 0.05 will be applied for statistical analysis.

#### Study 2

A thematic analysis of the data from the semi-structured interviews will be conducted using NVivo 15 software. Moreover, the findings from the Rorschach test will be analyzed using a methodology for interpreting projective material [48], with the aim of highlighting underlying psychic processes, particularly those related to attachment dynamics early traumas, the defensive mechanisms of participants. Additionally, the interviews reported from the AAI assessment will be coded by MN and AF under the supervision of a certified reliable coder [name] using the Adult Attachment Scoring and Classification System [49].

#### Study 3

For the group intervention, a Bonferroni correction will be applied to all *p*-values in t-tests. Cronbach’s alpha will be used to assess the reliability of the scales. Various analyses will be conducted to evaluate pre- and post-intervention effects as well as dose-response effects, including Student’s t-tests, repeated-measures ANOVA, and linear regression.

Primary and secondary outcomes will be analyzed using linear mixed models, incorporating a random group effect if estimation permits. The primary outcome measure is the variation in the total score on the ATSPPH-S at 9 months, calculated using dimensional scoring algorithms. Changes in the primary outcome and the relative effectiveness of the four intervention modalities will be assessed using mixed regression models, utilizing all available data while accounting for participant, time, and group levels. The underlying distribution for the mixed regression model will be determined based on residual distribution.

Per-protocol analyses will also be performed to test robustness. ANCOVA analyses may be conducted as needed to control for confounding variables that could influence the results. If data distribution is non-parametric, analyses such as Mann-Whitney, Wilcoxon, and Kruskal-Wallis tests will be employed.

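### Study 1's 5% margin of error holds only for a simple random sample, and an open e-mail invitation with voluntary response does not provide one

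*Protocol article*

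**What the plan says.** The sample size paragraph for Study 1 (Participants) starts from the source population: "We based our calculations on an approximate population size of 60,000 young individuals supported throughout the previous year". It then fixes the precision: "The margin of error was set at 5%, with a confidence level of 95" per cent. The method is named: "We applied Cochran’s formula (Z² × p × (1-p) / E²) to determine the required sample size". The conclusion is that "the sample size necessary for this cross-sectional study is 382 respondents".

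The Procedures section for Study 1 describes how respondents are obtained. "Recruitment will be facilitated via email distribution", and "Young residents of Youth transition Centers across the country will receive an email from the National Union for Youth Housing". The e-mail carries a link to a home page and a yes/no consent question. "Participants who select “Yes” will activate the questionnaire and proceed with the study", and those who answer no cannot take part. No random draw of residents or of residences is described.

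Table 1 requires Study 1 participants to live in a housing centre and lists substance use prevalence first among the main outcomes. The Data analysis section for Study 1 plans "descriptive and multivariate analyses (e.g., Chi-square/Fisher’s exact tests, correlation tests, ANOVA, etc".

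**The concern.** A sampling margin of error describes how far an estimate varies over repeated random draws from a defined population. Cochran's formula adds the assumption that each respondent is drawn independently. The Participants section claims that precision, while the Procedures section describes respondents who select themselves. A later analysis plan could change the variance estimator, but it could not turn volunteers into a random sample.

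The matter bears on a main outcome, because a prevalence is exactly the kind of estimate to which the 5% margin refers. Response related to the outcome is plausible on the article's own account: the Background reports stigma and reluctance to seek psychological care among these residents, and mistrust of institutions among migrant populations. A prevalence reported with a margin of 5 points for a source population of 60,000 would claim more than the data can support.

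A second, weaker issue is that respondents share residences. If answers are alike within a residence, intervals and tests that treat all respondents as independent may understate uncertainty.

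**Working it through.** **Inputs from the article (Participants, Study 1):** N = 60,000; E = 0.05; 95% confidence, so z = 1.96; stated n = 382. The article gives no p; I take p = 0.5, the worst case and the value that reproduces 382.

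**Reproducing 382.**
- n0 = z² × p(1 − p) / E² = 1.96² × 0.25 / 0.05² = 384.1.
- With finite-population correction: n = n0 / (1 + (n0 − 1)/N) = 384.1 / (1 + 383.1/60,000) = 381.7, rounded up to 382.

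The figure reproduces. The printed formula alone gives 385, so the correction was evidently applied.

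**Reserve in the figure.**
- Standard error = √(0.25/382) × √((60,000 − 382)/59,999) = 0.02558 × 0.9968 = 0.0255.
- Half-width = 1.96 × 0.0255 = 0.0500.

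The 5 points are used up under simple random sampling, with nothing left for any departure from it.

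**Self-selection (assumed bias).** If the estimate carries a fixed bias b, coverage of the nominal 95% interval is Φ(1.96 − b/SE) − Φ(−1.96 − b/SE).
- b = 2 points: b/SE = 0.78, coverage about 88%.
- b = 5 points: b/SE = 1.96, coverage about 50%.
- b = 10 points: b/SE = 3.92, coverage about 2.5%.

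A larger n shrinks SE but leaves b unchanged, so coverage gets worse.

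To show how little is needed for such a bias, suppose users respond r times as often as non-users. A true prevalence π is then estimated as πr / (πr + 1 − π). With r = 1.25, a prevalence of 30% is overestimated by 4.9 points and one of 50% by 5.6 points. With r = 0.8, they are underestimated by 4.5 and 5.6 points. The values of r are assumed, and the direction is unknown.

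**Nesting in residences (assumed cluster sizes and ICC).** Design effect = 1 + (m − 1) × ICC for m respondents per residence; half-width = 5.00 × √(design effect).

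| m | ICC | Design effect | Half-width (points) |
|---|---|---|---|
| 5 | 0.01 | 1.04 | 5.1 |
| 5 | 0.10 | 1.40 | 5.9 |
| 10 | 0.05 | 1.45 | 6.0 |
| 20 | 0.05 | 1.95 | 7.0 |
| 20 | 0.10 | 2.90 | 8.5 |

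A sparse national uptake points to the low end. The target is 382/60,000 = 0.64% of the population. With even uptake, a residence of 100 to 200 people (assumed) yields on average 0.64 to 1.27 respondents. If counts vary between residences as a Poisson variable, the design effect is 1 + mean × ICC. That is 1 + 0.64 × 0.05 = 1.03 up to 1 + 1.27 × 0.10 = 1.13, or a half-width of 5.1 to 5.3 points.

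**The case against.** The strongest reply is that the margin appears once, as a planning input; that the stated aim of Study 1 is mainly to identify associated factors and general trends; and that 382 is a reasonable target however it was reached. The article also commits to STROBE, its list of tests is open-ended, and its sociodemographic section is not itemised. Residence may therefore already be recorded, and cluster-robust methods are not excluded. Much of this stands. Silence on variance estimation or response reporting in a condensed article is not a fault. What it does not answer is the positive statement that 382 respondents give 5% at 95% confidence, alongside a recruitment route that cannot give it and a prevalence among the main outcomes.

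A reader might infer more than the article supports, in four ways.

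- **That Study 1 is a cluster sample whose true margin is 6 to 7 points.** No residences are sampled, and no ICC, cluster size or number of centres is given. Ten or 20 respondents per residence would mean that all 382 come from about 38 or 19 residences, for which a national deployment gives no support.
- **That the planned intervals and p-values will certainly be too narrow.** The effect of nesting may be negligible. For associations it depends on similarity within residences on both variables, so a design effect for prevalence does not carry over.
- **That the bias has been measured.** If respondents differ from non-respondents by 5 points, the error is 5 × (1 − 0.0064) = 4.97 points, but this only returns the assumed difference.
- **That 382 is miscalculated.** It is not.

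**Conclusion.** The concern holds for the precision claim. The arithmetic behind 382 is right, but the 5% margin belongs to a simple random sample, and the Procedures section describes volunteers answering an open national e-mail. This rests on the article's own text, with p = 0.5 as the only assumption needed to reproduce the figure.

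The size of the resulting error cannot be derived, because the article gives no response rate. The coverage figures (about 88% at a 2-point bias, about 50% at 5 points) show sensitivity and are not forecasts. Nesting in residences is a conditional remark: from negligible, about 5.1 points with few respondents per residence and a low ICC, to about 8.5 points with 20 per residence and an ICC of 0.10, every input assumed. The article supports no single replacement margin. Nor would a wider margin be valid under self-selection, since a design effect does not address bias.

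This should be changed. It does not threaten the conduct of Study 1, and 382 can stand as a target.

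**What to change.** - In Participants, Study 1, describe 382 as a recruitment target. State that 5% is a nominal best case under simple random sampling and covers neither non-response nor clustering. State p = 0.5, if that was the value used, and the finite-population correction.
- Do not present prevalence as nationally precise to within 5 points, and do not print 6% to 7% or any other replacement margin.
- Report the response fraction and, where population data exist, compare respondents with the source population.
- Where residence is recorded, use residence-robust variance for prevalence intervals and association tests.

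The cost is a less favourable precision statement and slightly more analysis work. No extra respondents are needed. The Trial status section says that recruitment has been under way since January 2025. If residence is not already on the questionnaire, adding it would come late and might need committee approval; the rewording and the response reporting do not depend on it.

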The longitudinal study will follow the same inclusion criteria as the qualitative study (Study 2). However, participation in the group sessions is open to all volunteers for each session, regardless of whether they are substance users. Informed consent will be systematically obtained before each session, ensuring fully informed participation. Promotion of the groups will be conducted through widespread dissemination of informational posters, email communications via the management of the partner structures, and during informational meetings. A follow-up meeting will be organized 15 days later to conduct the initial T0 evaluation with the volunteers.

The “Well-Being coffee group” intervention is implemented in several formats (see Fig. 1). Some groups will take place in person, others via videoconference, all conducted by the same psychologist throughout the sessions. Additionally, a control group will consist of participants who underwent the initial evaluation (T0) but did not attend any sessions. The inclusion of this control group allows for the assessment of changes in psychological and behavioral outcomes over time, comparing those who received the intervention to those who did not. The choice of this comparator was made based on feasibility and ethical considerations, ensuring that participants were not deprived of potential care while maintaining an adequate framework for evaluating the intervention’s effects. Across all formats, participation is voluntary, following a prior information phase and the signing of an informed consent form. Participants will complete standardized evaluation questionnaires at multiple time points (T0, T1, T2, T3).

The discussion groups aim to provide a supportive and open space for free expression. Their objective is to allow participants to articulate their thoughts, emotions, and personal experiences, as well as those evoked by group discussions on various themes, including identity, substance use, migratory experiences, and mental health. The impact of the intervention will be assessed regularly using standardized tools to measure levels of anxiety, depression, and changes in attitudes and willingness to seek help. Finally, a global satisfaction scale will be used at the end of the sessions to collect participants’ subjective feedback on their experiences within the groups (see Fig. 1).

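### Study 3 is sized for three modalities (3 × 55 = 165), but its primary analysis compares four

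*Protocol article*

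**What the plan says.** Three places in the protocol article bear on the number of groups in Study 3.

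- **Participants, Study 3.** The inputs are given as "we estimate a strong effect size of 0.7 (Cohen’s d) with a significance level of 0.05". From these and G*Power, "we determined that 55 participants would be required for each group modality, resulting in a total of 165 participants". Then: "To account for an estimated 10% dropout rate, we will include 182 young individuals in the study". The paragraph states neither the power nor whether the test is one- or two-sided.
- **Procedures, Study 3.** "Some groups will take place in person, others via videoconference, all conducted by the same psychologist throughout the sessions". In addition, "a control group will consist of participants who underwent the initial evaluation (T0) but did not attend any sessions". This section speaks of several formats and refers to Fig. 1, which was not available for this review.
- **Data analysis, Study 3.** The paragraph that defines the primary outcome (change in ATSPPH-S total score at 9 months) adds that "the relative effectiveness of the four intervention modalities will be assessed using mixed regression models".

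**The concern.** The sample-size paragraph and the analysis section both count modalities of the same study and reach different numbers: three by division, four by statement. The Procedures section does not settle it. It names two intervention formats, or three groups once the control is counted, and neither count gives four intervention modalities.

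Two things are at stake. First, the 55 per modality that the plan calls required would not be reached if the comparison really has four modalities. Second, a reader cannot tell from the text which groups enter the primary comparison, or whether the non-attending control is one of them. Left unsettled until the data are in, the grouping could be chosen with the results in view.

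**Working it through.** **Inputs.** From Participants, Study 3: d = 0.7, significance level 0.05, 55 per modality, 165 in total, 10% dropout, 182 enrolled. From Data analysis, Study 3: four modalities. Assumed because not stated: two-sided test, two-sample t-test, equal allocation, independent observations. Power is not stated, so 80%, 90% and 95% were tried.

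**Reproducing 55 per modality.** Solving the two-sample t-test (noncentral t) for n at d = 0.7 and two-sided 0.05:

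| Power | n per group |
|---|---|
| 80% | 34 |
| 90% | 44 |
| 95% | 55 (exact solution 54.02) |

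With n = 55 the power is 95.3%. A one-sided test at 0.05 gives 26, 36 and 45. Of the combinations tried at the stated level of 0.05, only two-sided with 95% power gives 55. The 95% is therefore an inference from the plan's figure and not a statement in the plan.

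**Number of modalities implied by the total.** 165 / 55 = 3.

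**Same rule with four modalities.**
- Evaluable: 4 × 55 = 220.
- Enrolled at 10% dropout: 220 / 0.90 = 244.4, so 245. That is 245 − 182 = 63 more than planned.

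**What 182 gives if spread over four.**
- Enrolled per modality: 182 / 4 = 45.5.
- After 10% loss: 45.5 × 0.90 = 40.95, about 41.
- Pairwise power at d = 0.7, two-sided 0.05, n = 41 per group: 87.9%, about 88%, against 95.3% at n = 55.
- Effect detectable with 95% power at n = 41 per group: d = 0.81.

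**Dropout allowance for the three-modality total.**
- The plan's 182 is reproduced by 165 × 1.10 = 181.5, rounded up.
- Losing 10% of 182 leaves 182 × 0.90 = 163.8, just under 165.
- Inflating so that 165 remain: 165 / 0.90 = 183.3, so 184. The difference is two participants.

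**The case against.** The best defence is that the formats may be listed in Fig. 1. The Procedures section speaks of several formats, which need not mean only two, and three formats at 55 each plus the control could loosely be called four. This stands as a caution: matching 165 to in-person, videoconference and control is an inference, and it would go too far to say that the protocol nowhere defines its groups. It does not remove the contradiction. If the figure shows four modalities, the total of 165 needs correcting or explaining; if it shows three, the word four in the analysis section does. Nor is this detail that an article may leave to a fuller document, because two published statements disagree.

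It is also fair to say that the t-test power is not the power of the planned analysis. The primary outcome goes to mixed models that use all available repeated data. Participation is voluntary and the control consists of people who attended nothing, so equal group sizes are not assured. The 88% therefore indicates scale only. Repeated measurements could raise the power; the group-level variation that the plan intends to model could lower it.

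Two stronger readings are tempting. A reader might apply a Bonferroni correction over all six pairwise comparisons and report a much larger loss of power. The plan attaches Bonferroni to t-tests and analyses the primary outcome with mixed models, and it sets no six-comparison family for that outcome. A reader might also add the control to four modalities and divide 182 by five. No passage says that there are five groups.

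Finally, the dropout slip is true but amounts to two participants and would not merit a separate point.

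**Conclusion.** The contradiction between three and four modalities holds, and one of the two sections must change. The text does not show which is the slip. The Procedures section fits three groups if the control is counted as a modality, in which case the error is one word and the sample size is unaffected. If four is right, the plan's own rule calls for 220 evaluable (245 enrolled) against 165 (182).

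In the four-modality case, keeping 182 gives about 41 evaluable per modality and about 88% pairwise power at d = 0.7, so the study is not badly underpowered for the effect it assumes. That figure is conditional on equal allocation, independent observations and a two-sided 0.05 two-sample t-test. Calling it a fall from 95% rests further on the inferred design power. The main fault is that the stated requirement and the stated comparison do not belong to the same design.

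**What to change.** State one number of modalities for Study 3, say whether the non-attending control is counted, and use that number in the Participants, Procedures and Data analysis sections and in Fig. 1.

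- **If three:** change four to three in the Data analysis section. If the control is one of the three, do not call all of them intervention modalities.
- **If four:** keep enrolment at 182 and restate it as about 41 evaluable per modality, with about 88% pairwise power at d = 0.7 (detectable d about 0.81 at 95% power), giving the assumptions listed above.

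In the same edit, under the three-modality reading, either set enrolment at 184 or state that 182 leaves about 164 after 10% dropout. State the power and sidedness that were entered in G*Power, so that 55 can be reproduced without inference.

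The cost is a text correction. Neither branch requires extra enrolment, apart from two participants if 184 is chosen. The article reports that recruitment is under way, so the number should be fixed before any outcome data are analysed, and if the change counts as substantial it needs the ethics committee approval that the protocol itself requires.
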